## Abstract

**Background:**

Acute left-sided colonic obstruction is most often caused by malignancy and the surgical treatment is associated with a high mortality and morbidity rate. Moreover, these operated patients end up with a temporary or permanent stoma. Initial insertion of an enteral stent to decompress the obstructed colon, allowing for surgery to be performed electively, is gaining popularity. In uncontrolled studies stent placement before elective surgery has been suggested to decrease mortality, morbidity and number of colostomies. However stent perforation can lead to peritoneal tumor spill, changing a potentially curable disease in an incurable one. Therefore it is of paramount importance to compare the outcomes of colonic stenting followed by elective surgery with emergency surgery for the management of acute left-sided malignant colonic obstruction in a randomized multicenter fashion.

**Methods/design:**

Patients with acute left-sided malignant colonic obstruction eligible for this study will be randomized to either emergency surgery (current standard treatment) or colonic stenting as bridge to elective surgery. Outcome measurements are effectiveness and costs of both strategies. Effectiveness will be evaluated in terms of quality of life, morbidity and mortality. Quality of life will be measured with standardized questionnaires (EORTC QLQ-C30, EORTC QLQ-CR38, EQ-5D and EQ-VAS). Morbidity is defined as every event leading to hospital admission or prolonging hospital stay. Mortality will be analyzed as total mortality as well as procedure-related mortality. The total costs of treatment will be evaluated by counting volumes and calculating unit prices. Including 120 patients on a 1:1 basis will have 80% power to detect an effect size of 0.5 on the EORTC QLQ-C30 global health scale, using a two group t-test with a 0.05 two-sided significance level. Differences in quality of life and morbidity will be analyzed using mixed-models repeated measures analysis of variance. Mortality will be compared using Kaplan-Meier curves and log-rank statistics.

**Discussion:**

The Stent-in 2 study is a randomized controlled multicenter trial that will provide evidence whether or not colonic stenting as bridge to surgery is to be performed in patients with acute left-sided colonic obstruction.

**Trial registration:**

Current Controlled Trials ISRCTN46462267.

## Background

Colorectal cancer is the second most common cancer in women and the third most common in men in the Netherlands [1]. The incidence in the Netherlands in 2003 was 9898 new cases, men and women were equally affected (Dutch Cancer Registry) [2]. Literature shows that between 7 and 29% of the patients present with a sub-total or total bowel obstruction [3,4].

Conventionally these patients are treated with emergency surgery to restore luminal patency. These emergency operations, involving an unprepared and obstructed bowel, include a variety of procedures ranging from a loop colostomy (blow-hole) to a Hartmann's procedure or even a subtotal colectomy. These interventions have a mortality rate of 15–34% and a morbidity rate of 32–64% despite advances in perioperative care [4-8]. It is well recognized that in a considerable number of these patients the ostomies will not be closed because of old age, metastatic disease or poor condition [3,7]. Patients with a permanent stoma do report a significant lower health-related quality of life than comparable patients without colostomy and require costly stoma material [9-12].

Since the early 1990s colonic stenting has been introduced, mainly in the left-sided colon, to restore luminal patency. It can be applied as a preoperative treatment to prepare patients for elective surgery as well as a definitive palliative procedure in patients with incurable disease [13]. In uncontrolled studies stent placement before elective surgery has been suggested to improve the patients' clinical condition, decreasing mortality, morbidity and number of colostomies [4,5,7,8]. Additionally this temporary procedure gives the opportunity to perform accurate tumor staging, leading to avoidance of surgery in patients with disseminated disease or unacceptable surgical risk [7,14-16]. In these patients the colonic stent may serve as permanent palliation. Colonic stenting also creates the opportunity to give neo-adjuvant therapy, improving patients' prognosis.

A systematic review by Sebastian et al. of 54 uncontrolled trials and case reports on placement of self-expandable metal stents revealed a technical success rate of 90–100%, a clinical success rate of 84–94% and clinical success when used as bridge to surgery of 71.7%. Major complications related to stent placement include perforation (4%), stent migration (11.8%) and re-obstruction (7.3%), causing a cumulative mortality of 0.58% [13]. It has to be underlined that stent perforation can lead to peritoneal tumor spill, changing a potentially curable disease in an incurable one. Minor complications like rectal bleeding (5%), transient anorectal pain (5%) and fecal impaction can mostly be managed conservatively [17,18].

The overall influence of colonic stenting on patient's quality of life is unknown. It is important to realize that stenting so far has mainly been done by experts and the published results are mostly uncontrolled, subjective to selection bias and do not include the learning curves.

To date a randomized comparison between the treatment with self-expandable stents before elective surgery and emergency surgery for malignant acute colorectal obstruction has not been published. We propose to compare these two treatment algorithms in a prospective multicenter randomized setting in terms of effectiveness (primary outcome measure) and healthcare costs.

## Methods/design

### Study objectives

To compare, in a prospective randomized fashion, colonic stenting followed by elective surgery with emergency surgery for the management of acute left-sided malignant colonic obstruction in terms of effectiveness. Effectiveness will be evaluated in terms of quality of life, morbidity and mortality.

### Study design

The Stent-in 2 study is a randomized multicenter trial with 4 academic and 11 regional hospitals participating in the project. Patients presenting with confirmed acute left-sided malignant colonic obstruction will be asked for informed consent if the inclusion and exclusion criteria are met. Computerized randomization will take place after informed consent has been obtained. Randomization will be performed centrally at the Academic Medical Center, using computer-generated lists prepared by the Department of Clinical Epidemiology and Bio-statistics. Lists will be constructed with randomly permuted blocks per stratum, in which strata will be defined by center (participating hospital). Patients will be randomized to either emergency surgery (current standard treatment) or colonic stenting as bridge to elective surgery (figure 1). Treatment will be initiated within 24 hours after randomization.

**Figure 1 F1:**
[figure not shown]
Flowchart Stent-in 2 study.

### Study population

The study population consists of patients with acute left-sided malignant colonic obstruction. Inclusion criteria are: symptoms of left-sided (colon descendens, sigmoid or rectum) malignant colonic obstruction existing less than one week, defined as obstructive symptoms with dilation of the colon on either plain abdominal X-ray and typical abnormalities on a gastrografin enema study or CT-abdomen with contrast compatible with a malignant colonic stricture; age above 18 years; signed informed consent. Exclusion criteria are: peritonitis, perforation, fever, sepsis or other serious complications demanding urgent surgery; American Society of Anesthesiologists (ASA) IV or V; obstruction due to non-colonic malignancies or from a benign origin: distal tumor margin less than 10 cm from the anal verge; incapability to complete self-report quality of life questionnaires.

### Outcome parameters

Effectiveness and costs of both strategies will be compared. Effectiveness will be evaluated in terms of quality of life, morbidity and mortality. Quality of life will be measured with the following standardized questionnaires: EORTC QLQ-C30 (European Organization for Research and Treatment of Cancer (EORTC) Quality of Life Questionnaire C30), the colorectal cancer specific EORTC QLQ-CR38 (European Organization for Research and Treatment of Cancer (EORTC) Quality of Life Questionnaire CR38), the EQ-5D (EuroQol 5 dimensions) and the EQ-VAS (EuroQol visual analogue scale). Morbidity is defined as every event leading to hospital admission or prolonging hospital stay. Mortality will be analyzed as total mortality as well as procedure-related mortality.

Cost items will include costs of hospital admissions and readmissions (operation, nursing days, outpatient visits), institutional care (nursing homes, hospice), home care, medication and other health care providers as well as direct non-medical costs (travel expenses).

### Participating centers

Fifteen Dutch hospitals including 4 academic and 11 non academic are currently participating in this trial. Specific requirement is to assure that enteral stent placement is performed by an experienced gastroenterologist. Gastroenterologists are considered experienced after placement of at least 20 enteral stents of which 10 colonic. In case no experienced gastroentorologist is available the patient should be referred to a nearby hospital with sufficient experience. The patient can always be referred for stent placement to the Academic Medical Center in Amsterdam. Laparoscopic sigmoidectomy or stoma creation is allowed if sufficient experience is available (> 20 cases).

### Ethics

This study is conducted in accordance with the principles of the Declaration of Helsinki and 'good clinical practice' guidelines. The protocol has been approved by the Medical Ethical Committee of the Academic Medical Center in Amsterdam and the local Ethical Committees of the participating centers. Prior to randomization informed consent will be obtained from all patients.

### Study outline

Patients presenting with confirmed acute left-sided malignant colonic obstruction will be asked for informed consent if the inclusion and exclusion criteria are met. Computerized randomization will take place after written informed consent has been obtained according to the Guidelines of Clinical Research in Humans. Randomization will be performed centrally at the Academic Medical Center, using computer-generated lists prepared by the Department of Clinical Epidemiology and Bio-statistics. Patients will be randomized to either emergency surgery or colonic stenting as bridge to elective surgery. Treatment will be initiated within 24 hours after randomization.

#### Colonic stenting

##### A) Material

For this study, the enteral stent which has been most frequently used in clinical studies will be employed (Enteral Wallstent™ (Boston Scientific, Natick, MA)) [13,18]. This through-the-scope stent is available in the length of 6 and 9 cm, with a diameter of 22 mm.

##### B) Procedure

After preparation of the distal colon with an enema, colonoscopy is performed. In all patients prophylactic antibiotics will be administered, covering aerobic and anaerobic bacteria. After endoscopic visualization of the lesion, biopsies will be taken and the length of the lesion will be measured (fluoroscopically). In case a normal colonoscope or sigmoidoscope can transverse the lesion there is no indication for stent placement and the patient will be considered a drop out. The obstructive lesion should not be dilated prior to stent placement. Stents will always be placed over a guidewire and under fluoroscopic guidance. A metallic, uncovered, self-expandable stent will be implanted, at least 3 cm longer (1,5 cm at both sides) than the lesion. If the stent does not cover the entire length of the tumor, a second overlapping stent will be placed. The correct position of the stent will be confirmed using fluoroscopy and endoscopy.

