##### C) Post-procedure

Successful decompression is defined as restoration of intestinal transit based on resolution of obstructive symptoms on plain abdominal X-ray, production of stools and/or resolution of nausea and vomiting. If successful decompression is achieved and the condition of the patient is stabilized, tumor staging of the disease will be performed (CT-scan/plain chest X-ray) within one week. If any of the following conditions will be present, patients will be considered not suitable for surgical therapy and the self-expandable stent will serve as a palliative therapy: patients at high risk due to persistent comorbidity, advanced pelvic disease, peritoneal carcinomatosis and/or unresectable metastatic lesions. If decompression is not achieved within time frame of 3 days, or if clinically required, patients will be treated surgically but will not cross over to the surgical arm in the analysis.

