#### Emergency surgery

##### A) Procedure

Patients will be operated according conventional standards within 24 hours after randomization. Whether a (palliative) resection or fecal deviation is done is at the discretion of the surgeon. Surgical options according to current standards are loop colostomy (blow-hole), resection with primary anastomosis with or without ileostomy, Hartmann's procedure, (sub)total colectomy with ileostomy or ileorectal anastomosis.

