### Statistical analysis

#### Intention to treat

The analysis will be performed in accordance with the intention to treat principle.

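### Stent-arm patients whose lesion a scope can pass are called drop-outs after randomization, with nothing said on follow-up or analysis, which conflicts with the intention-to-treat statement

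*Protocol article*

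**What the plan says.** All references are to the protocol article.

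- **Order of events.** Under Study design: "Computerized randomization will take place after informed consent has been obtained". Under Study population, eligibility rests on symptoms and imaging; no endoscopic finding is required.
- **Stent arm.** Under Colonic stenting, B) Procedure: "After preparation of the distal colon with an enema, colonoscopy is performed". The rule at issue follows in the same section. For a patient whose lesion lets a standard scope through, it reads: "there is no indication for stent placement and the patient will be considered a drop out". The term is not defined there or elsewhere in the article.
- **Surgery arm.** Under Emergency surgery, A) Procedure: "Patients will be operated according conventional standards within 24 hours after randomization". No endoscopy and no corresponding rule is described.
- **Analysis principle.** Under Intention to treat: "The analysis will be performed in accordance with the intention to treat principle". No exception is given.
- **A neighbouring case.** Under Colonic stenting, C) Post-procedure, when decompression fails or surgery is clinically required, "patients will be treated surgically but will not cross over to the surgical arm in the analysis".

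**The concern.** A patient is randomized, allocated to stenting, and only then examined with a scope. If the scope passes, the patient is given a label that ordinarily means leaving the study. A surgery-arm patient with an equally passable lesion is never examined for it and stays in. If the label means removal from the analysis, the exclusion rests on a post-randomization finding that, as described, can arise in one arm only and is made by an endoscopist who knows the allocation.

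The label may also mean that follow-up stops. The week 4, 12 and 24 questionnaires and the two-weekly telephone calls (Data collection and monitoring) and the cost items (Economic evaluation) would then not be collected. The available-data approach to missing values (Data analysis) would leave these patients with at most a baseline quality-of-life record, and the mortality comparison would lose or censor them in one arm. A later analysis plan could not recover those data. Quality of life, morbidity, mortality and cost would all be exposed.

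**Working it through.** **1. The passages side by side**

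| Question | Stent arm | Surgery arm |
|---|---|---|
| Is passability assessed before randomization? | Not required | Not required |
| Is it assessed after randomization? | Yes, at the stent colonoscopy | Not described |
| Consequence if passable | Patient is called a drop-out | None; the finding is not made |
| Statement that the patient stays in follow-up or analysis | None specific to this group | Not needed |

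For failed decompression the article states which arm the patient is analysed in. For the passable lesion it does not. Only the general intention-to-treat statement applies, and the drop-out label in its ordinary sense contradicts it.

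**2. The plan's own figure**

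Inputs from Sample size calculation: 120 patients, 1:1 (60 per arm), effect size 0.5, two-group t-test, two-sided 0.05, stated power 80%.

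- Noncentral t, 60 v 60: power 77.5%.
- Normal approximation, 60 v 60: power 78.2%.

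The stated 80% is not quite reached with the named test. That is a separate matter and the present point does not depend on it. I use 77.5% as the reference.

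**3. Size if the rule means exclusion**

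The documents give no share of passable lesions and no outcome difference. Both are assumptions:

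- d = share of stent-arm lesions that a scope can pass: 5% or 10%.
- g = how much better these patients do than the rest of the stent arm: 0.25, 0.5 or 1.0 SD.

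The full stent-arm mean is the mean of the non-passable patients plus d × g. Removing the passable patients therefore shifts the stent-arm mean by −d × g. The remaining stent arm has 60 × (1 − d) patients: 57 at 5%, 54 at 10%. Power is for a true effect of 0.5 SD in favour of stenting, so the apparent effect is 0.5 − d × g.

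| d | Stent n | g (SD) | Bias (SD) | Bias / 0.5 | Power (t-test) |
|---|---|---|---|---|---|
| 0 | 60 | – | 0 | 0 | 77.5% |
| 5% | 57 | 0 | 0 | 0 | 76.4% |
| 5% | 57 | 0.25 | −0.0125 | 2.5% | 74.3% |
| 5% | 57 | 0.5 | −0.025 | 5% | 72.1% |
| 5% | 57 | 1.0 | −0.05 | 10% | 67.5% |
| 10% | 54 | 0 | 0 | 0 | 75.3% |
| 10% | 54 | 0.25 | −0.025 | 5% | 70.9% |
| 10% | 54 | 0.5 | −0.05 | 10% | 66.2% |
| 10% | 54 | 1.0 | −0.10 | 20% | 56.1% |

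The rows with g = 0 isolate the loss of numbers: 77.5 − 75.3 = 2.2 percentage points at 10%. In the rows with g = 0.5 or 1.0, selection costs more than the lost numbers. With no true effect, the same biases raise the two-sided type I error from 5% to between 5.05% (d = 5%, g = 0.25) and 8.3% (d = 10%, g = 1.0), by the normal approximation.

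If these patients do worse than the rest, g is negative and the bias favours the stent arm.

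**The case against.** The strongest objection is that the article nowhere says these patients are left out of the analysis. The term is undefined, stands in a clinical procedure section, and directly follows the remark that a stent is not indicated. It could mean only that the patient leaves the stenting pathway. The statements on intention to treat and on six months of follow-up carry no exception, and the handling of failed decompression can be read as showing that the authors do keep deviating patients in their arm. A definition could also sit in the full protocol, which is not shown.

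This stands as far as it goes. A reader might infer that the plan breaks intention to treat outright; the text supports only a conflict between one rule, in its ordinary meaning, and the stated principle. It does not remove the point: no passage says that these patients are retained, and the article does say so for a neighbouring group.

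A reader might also infer that the rule removes the mildest obstructions and so works against stenting. That is plausible, since a passable lesion suggests a less complete obstruction. But the article does not grade obstruction or link scope passage to any outcome, so the prognostic role and the direction are both inferences.

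Larger biases can be computed. If passable patients were exactly the best-outcome tail, the shift is φ(z)/(1 − p), which gives 0.109 SD at 5% and 0.195 SD at 10%. Halving these for a correlation of 0.5 gives about 0.054 and 0.0975 SD, which still implies that passable patients score 0.054/0.05 = 1.09 SD and 0.0975/0.10 = 0.98 SD better than the rest of the arm. That is about twice the 0.5 SD the trial takes as clinically meaningful, and nothing in the documents supports it as a central case.

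**Conclusion.** The point holds as an inconsistency that must be reconciled. The drop-out rule comes after randomization, is described in one arm only, and in its ordinary meaning conflicts with the intention-to-treat statement. It is also out of line with the handling of failed decompression. It is a stated rule, not detail left to another document.

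The consequence is conditional. If the label means exclusion or the end of follow-up, the arms are selected differently on a plausibly prognostic finding. With an assumed 5–10% share and an assumed 0.25–1.0 SD better outcome, the bias in the stent-arm mean is about 0.01–0.10 SD, or 2.5–20% of the 0.5 SD target, probably but not certainly against stenting. The loss of numbers alone is small. If the label means only that no stent is placed, intention to treat is intact and the wording alone needs correcting.

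**What to change.** In Colonic stenting, B) Procedure, replace the drop-out wording with a statement that a randomized patient in whom no stent is placed because the scope passes:

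- stays in follow-up, with the week 4, 12 and 24 questionnaires, the telephone calls and the cost items; and
- is analysed in the stent arm as randomized.

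Any analysis without these patients should be secondary and labelled as a non-randomized comparison.

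The cost is one sentence in the protocol and continued follow-up of a few patients (3 to 6 of 60 under the assumed 5–10%) through the existing schedule and trial nurse. The change concerns follow-up and analysis only; how these patients are treated is not addressed here.

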##### C) Post-procedure

Successful decompression is defined as restoration of intestinal transit based on resolution of obstructive symptoms on plain abdominal X-ray, production of stools and/or resolution of nausea and vomiting. If successful decompression is achieved and the condition of the patient is stabilized, tumor staging of the disease will be performed (CT-scan/plain chest X-ray) within one week. If any of the following conditions will be present, patients will be considered not suitable for surgical therapy and the self-expandable stent will serve as a palliative therapy: patients at high risk due to persistent comorbidity, advanced pelvic disease, peritoneal carcinomatosis and/or unresectable metastatic lesions. If decompression is not achieved within time frame of 3 days, or if clinically required, patients will be treated surgically but will not cross over to the surgical arm in the analysis.

##### D) Elective surgery after stenting

Candidates for elective surgery will be operated on after completion of the preoperative screening, preferably between day 5 and 14 after inclusion, at the latest four weeks after inclusion. If possible and convenient, patients will be discharged between diagnostic work-up and surgery. After preoperative bowel preparation and administration of antibiotics both according to the hospital protocol resection of the tumor will be performed, the extension of which will be determined by the specific characteristics of the malignant process. During surgical exploration, the position and efficacy of the stent will be evaluated.

